#### Time-to-event outcomes

These will be summarized by the median and interquartile range in each treatment group and compared using Cox’s proportional hazards models, with treatment comparisons presented as hazard ratios and 95% confidence intervals. Such models require an assumption of proportional hazards to be met. Any patients with a time of zero (for example, the duration of post-randomization stay in an intensive care or high dependency unit might be zero if the patient was randomized after being discharged from the intensive care or high dependency unit) will be included in analyses by assuming a time of half of the smallest non-zero time to the event. Appropriate censoring variables will be used, as given in Table 3.

**Table 3 Tab3:** **Censor variables for time-to-event outcomes**

**Outcome**	**Censor variable**
Time from randomization to first occurrence of primary outcome	Date of 3 month follow-up questionnaire, if completed
	Date of death, for patients who die prior to 3 month follow-up
	Date of discharge from hospital, for patients who survive 3 months postoperatively but do not complete the follow-up questionnaire (which captures primary outcome events after hospital discharge)
Duration of post-randomization stay in intensive care or high dependency unit	Time of death in intensive care or high dependency unit
Duration of postoperative hospital stay	Time of death in hospital
Time to death	Time of last follow-up (usually 3 months post-operation)

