**Table 2 Tab2:** **Classification of primary and secondary outcomes**

**Category**	**Outcomes**
Binary outcome measures	• Primary outcome measure: proportion of patients experiencing an infectious or ischaemic event
	The following secondary outcome measures:
	• Proportion of patients experiencing an infectious event
	• Proportion of patients experiencing an ischaemic event
	• Use of activated factor seven
	• Use of Human Blood Coagulation Factor IX
	• Significant pulmonary morbidity
Continuous outcome measures	The following secondary outcome measures:
	• Units of RBCs transfused
	• Fresh frozen plasma transfusions
	• Cryoprecipitate transfusions
	• Platelet transfusions
Time-to-event outcome measures	The following secondary outcome measures:
	• Time from randomization to first occurrence of the primary outcome measure (secondary analysis of the primary outcome measure)
	• Duration of post-randomization stay in intensive care or high dependency unit
	• Duration of post-randomization hospital stay
	• Time from randomization to death from any cause
Continuous longitudinal outcome measures	The following secondary outcome measures:
	• EQ5D single summary index score
	• EQ5D visual analogue scale score

General presentation and analysis techniques for each type of outcome are described next.

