### Pre-specified ancillary analyses

There are three pre-specified ancillary observational analyses in the study protocol:Estimating the relationship between the number of RBC units transfused, and the risk of the primary outcome or death from any cause, stratified by trial arm.Investigating the relationship between percentage decline in haemoglobin concentration from the preoperative level and the risk of primary outcome or death from any cause, taking into account the number of RBC units transfused.Investigating whether the age of the RBCs is associated with the risk of primary outcome or death from any cause.

To address analyses (a) and (b), three logistic regression models will be fitted with the following explanatory variables:Total number of RBC units transfused (either pre- or post-randomization)Percentage decline in haemoglobin concentration from the preoperative levelTotal number of RBC units transfused and percentage decline in haemoglobin concentration.

To address analysis (c), the age of the ‘oldest’ unit of RBCs received by a patient will be fitted as an explanatory variable. The age will be determined by linking the donation numbers of all RBCs transfused to a blood bank database and retrieving the date of donation.

In all of these models, adjustment will be performed for any variables found to be potential confounders, defined as: variables associated with both the exposure and the outcome that are not an intermediary step on the causal pathway between the exposure and outcome, that significantly contribute to the relevant multivariable model (defined as a likelihood ratio *P* value <0.05 or by modifying the effect estimate by greater than 10%). In analyses (a) and (b), the following variables have been identified as possible confounders: randomized allocation, operation type, centre (as a random effect), EuroSCORE, age and sex. Likewise for analysis (c), number of RBC units transfused, blood group, EuroSCORE, age and sex have been identified. For analyses (a) and (b), the instrumental variable method of controlling for confounding will also be explored, using randomized allocation as the instrumental variable [18].

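### Table 3 censors stay and time to first primary event at death without naming the estimand; the median/IQR rule and the hospital-stay clock also need correcting

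*SAP article*

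**What the plan says.** The section on time-to-event outcomes specifies Cox "proportional hazards models, with treatment comparisons presented as hazard ratios and 95% confidence intervals" and adds: "Appropriate censoring variables will be used, as given in Table 3". Table 3 then uses death as censoring in three of its four rows:

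- ICU/HDU stay: "Time of death in intensive care or high dependency unit".
- Hospital stay: death in hospital.
- Time to first primary event: "Date of death, for patients who die prior to 3 month follow-up", as one of three censoring dates.

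Under Outcomes, the primary composite covers infectious and ischaemic events; death is not a component. Table 2 labels time to first primary event as a secondary analysis of the primary outcome and lists time to death from any cause as its own outcome. The checks named under Model assumptions are residual plots and log-log plots. None of the listed sensitivity analyses concerns death. Death joined to the primary outcome appears only in the observational ancillary analyses, which study "the risk of the primary outcome or death from any cause".

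On presentation, the time-to-event section says: "These will be summarized by the median and interquartile range in each treatment group". On the clock, Table 2 has "Duration of post-randomization hospital stay" and Table 3 has "Duration of postoperative hospital stay".

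**The concern.** A patient who dies in hospital can never be discharged alive. Under Table 3 that patient leaves the risk set at death, exactly like someone whose observation merely stopped. The same happens to a patient who dies before having a primary event. The Cox model then estimates a cause-specific HR, that is, the rate of discharge (or of the event) among those still alive and at risk. Deaths in one arm do not count against it. If those who die would have stayed longest or were most likely to have an event, removing them leaves a healthier risk set, and the HR shifts towards the arm with more deaths.

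Mortality is an outcome the thresholds might affect, so this matters most when the strategies differ in safety. The plan names no estimand and no competing-risk summary, and the plots it lists would not reveal the problem. A reader of the stay results would not know that death had been set aside.

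**Working it through.** **1. The plan's own figure.** The article gives 1,468 patients for 17% v 11%, 90% power and two-sided 5%. With the pooled two-proportion formula, n′ = [1.960·√(2·0.14·0.86) + 1.2816·√(0.17·0.83 + 0.11·0.89)]² / 0.06² ≈ 701 per arm. With continuity correction, n = (n′/4)·[1 + √(1 + 4/(n′·0.06))]² ≈ 734, and 2 × 734 = 1,468, an exact match. This confirms the 17% and 11% used in step 4. It has no bearing on the time-to-event analyses, for which the article gives no figure.

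**2. Effect of the censoring rule, first set of assumptions.** One million simulated patients; both arms have identical underlying stay and event processes, so only mortality differs. Assumed: 15% of patients are high-risk; mean stay is 20 v 7 days; 90-day event risk without death is 50% v 10.8% (0.15·0.50 + 0.85·0.108 ≈ 17% overall); deaths occur only in the high-risk group. HRs are for the higher-mortality arm v the other.

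| Mortality | Discharge HR, Table 3 | Discharge HR, dead kept as never discharged | Primary-event HR, Table 3 | HR for event or death |
|---|---|---|---|---|
| 3% v 3% | 1.000 | 0.999 | 0.999 | 0.998 |
| 2% v 4% | 1.007 | 0.952 | 0.961 | 1.062 |
| 3% v 6% | 1.007 | 0.933 | 0.950 | 1.104 |
| 3% v 10% | 1.011 | 0.860 | 0.871 | 1.226 |

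If death is instead unrelated to prognosis, the Table 3 HR stays at about 1.00 throughout. The alternatives still move against the higher-mortality arm (0.955 to 0.876 for stay; 1.110 to 1.376 for event or death).

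**3. Second set of assumptions, stay only.** 2,000 patients per trial, 1,000 trials per scenario; 10% sick, with stay 5 + Exp(mean 20) days; others 4 + Exp(mean 4) days; deaths only among the sick, on days 1–15.

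- In-hospital mortality 1.7% v 3.4%: HR 1.023 under Table 3, 0.961 with the dead as never discharged.
- In-hospital mortality 1.7% v 4.2%: HR 1.036 and 0.947.

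For scale, with nearly all 2,000 patients discharged, SE(log HR) ≈ 2/√2000 = 0.045. The largest stay shift, ln 1.036 = 0.035, is below one SE. A nominal 5% test of no stay difference would reject in 8.9% and 12.7% of trials in these two scenarios.

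For the primary event in step 2, with 1,000 patients per arm:

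- 2% v 4%: 161 + 153 = 314 events, SE ≈ 2/√314 = 0.113, shift ln 0.961 = −0.040, about 0.35 SE.
- 3% v 10%: 157 + 132 = 289 events, SE ≈ 0.118, shift ln 0.871 = −0.138, about 1.2 SE.

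**4. Median and IQR.** A first quartile of time to event exists only if at least 25% of an arm have the event; a median needs 50%. The planned 17% and 11% are both below 25%, so no quartile is reached. For death, 3-month mortality would have to reach 25% for even the first quartile. The article gives no mortality figure; the highest assumed above is 10%.

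**5. Clock.** For hospital stay, Table 2 says post-randomization and Table 3 says postoperative. Under Flow of participants, randomization can happen at any point after surgery once the haemoglobin or haematocrit criterion is met, so the two durations differ. For ICU/HDU stay, Table 2, Table 3 and the time-to-event text all say post-randomization. The list under Outcomes calls both stays postoperative.

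**The case against.** The strongest reply is that censoring at death in a Cox model is standard and estimates a well-defined quantity. Choosing between cause-specific and subdistribution hazards is a choice of estimand, and the article never claims that its HR describes a world without death. That stands: the defect is the missing label and the missing companion summary, not the model.

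The reply continues that the alternative is not the truth either. With identical underlying stay, the never-discharged analysis also departs from 1.00 (0.947 and 0.961 in step 3), because it combines mortality with stay, and mortality already has its own randomized comparison. This also stands, and is why the alternative belongs beside the planned HR and not in its place.

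Three stronger readings are tempting, and the article does not support them.

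- A reader might infer that the stay results will point the wrong way when one strategy is harmful. The computed shift is small, and it needs both a mortality gap and deaths concentrated in the sickest patients.
- A reader might infer that the primary comparison is compromised. It is a logistic regression on a binary composite and does not use Table 3.
- A reader might infer that the authors had adopted event-or-death as a composite and left it out of the randomized comparison. The ancillary wording can mean one composite or two separate outcomes, and the nested case-control proposal defines cases by the primary outcome event alone. The absence of a randomized version contradicts nothing in the plan.

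**Conclusion.** The point holds for secondary analyses only. Table 3 censors three outcomes at death without naming the estimand, and nothing else in the article offsets this. The HR gives no penalty to the arm with more deaths. If deaths fall mainly in high-risk patients, it favours that arm by about 1–4% for stay and about 4–13% for time to primary event. If deaths are unrelated to prognosis, there is no shift. Every mortality, stay and dependence input behind these sizes is an assumption.

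Two further faults need no simulation. The median/IQR rule cannot be carried out for time to primary event at the planned rates, or for death at any plausible mortality. The hospital-stay label conflicts between Tables 2 and 3. A reader might extend that conflict to every stay clock, but the two tables agree on ICU/HDU stay.

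**What to change.** - Keep the death-censored HRs and label them cause-specific.
- Add a supportive analysis of time to discharge alive with death as a competing event: cumulative incidence curves, or patients who die kept in the risk set as never discharged. State that it combines mortality with stay.
- Add primary outcome or death from any cause as a randomized sensitivity analysis.
- Measure hospital stay from randomization in both tables.
- For death and the primary event, replace median and IQR with 3-month Kaplan–Meier or cumulative-incidence percentages by arm.

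All of this uses data already collected. The cost is a little extra analysis and one HR that is slightly harder to explain. The Discussion states that the plan has already been executed, so the added analyses should be labelled post hoc.

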#### Continuous longitudinal outcomes

These will be compared using a linear mixed-effects methodology with the treatment group and study design variables fitted as fixed effects, and patient terms as random effects. Separate parameter estimates will be incorporated into models for: (a) the mean baseline response across both treatment groups and (b) each post-randomization time point for each treatment. This approach of ‘jointly’ modelling the baseline and post-intervention measurements avoids the necessity of either excluding cases with missing baseline measures or imputing missing baseline values. If the time by treatment interaction (post-intervention) is not statistically significant at the 10% level, an overall treatment effect will be reported. If the interaction is statistically significant, the changes in treatment effect with time will be described. Different variance/covariance structures will be explored (compound symmetry, first-order auto-regressive, Toeplitz and unstructured), and the structure that provides the best fit using the likelihood ratio test (or Akaike information criterion if compared models are not nested) will be used. Treatment comparisons will be presented as adjusted differences in means with 95% confidence intervals.

### Adjustment in models

The intention is to adjust all models for factors included in the cohort minimization: operation type (four different types) as a fixed effect and centre (17 different centres) as a random effect (or a shared frailty term in time-to-event models). Occasionally, the operation type might differ between the study database and the randomization system because it has been entered incorrectly into the randomization system. In this case, the value from the study database will be used, as the operation type recorded on the database will have been confirmed to be correct in such instances. For all treatment comparisons, the liberal group will be the reference group.

### Statistical significance

For hypothesis tests, two-tailed *P* values <0.05 are considered statistically significant. Likelihood ratio tests will be used in preference to Wald tests for hypothesis testing.

### Model assumptions

For all methods outlined, underlying assumptions will be checked using standard methods, for example, residual plots or log-log plots for proportional hazards. If assumptions are not valid, alternative methods of analysis will be sought (for example, by applying a logarithmic transformation or fitting a two-part mixed model for semi-continuous data [11]). If extreme outlying observations are found, whereby inclusion of such values results in an inadequate model fit, such observations will be excluded from the main analyses and sensitivity analyses may be performed to examine the effect on the study’s conclusions.

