### Patient population

The analysis population will consist of all randomized patients, excluding: (a) patients marked as ‘randomized in error’ and (b) withdrawn patients who were unwilling for data collected to be used. Randomization in error is expected to happen rarely (<10 patients); it occurs when a member of research staff realizes shortly after randomization and prior to any intervention that a randomized participant is not in fact eligible. All study analyses will be performed on a modified intention-to-treat basis (including all randomized patients, with the exception of withdrawn patients or those with missing outcome data).

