#### Continuous outcomes

These will be summarized by the mean and standard deviation (or median and interquartile range if data are skewed) in each treatment group and compared using linear regression. For untransformed data, treatment comparisons will be presented as adjusted differences in means with 95% confidence intervals, and for logarithmically transformed data as adjusted ratios of geometric means with 95% confidence intervals. If a logarithmic transformation is not satisfactory other analysis or presentation methods will be sought.

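### Extreme values that spoil model fit must be dropped from the main analysis of secondary outcomes, whether errors or genuine, with only an optional check

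*SAP article*

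**What the plan says.** The rule is in the SAP article under Model assumptions. For extreme outlying observations it sets one trigger, a poor fit when they are included, and one action: "such observations will be excluded from the main analyses and sensitivity analyses may be performed". So exclusion is mandatory and the check on it is not.

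Three other places bear on this.

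- **Patient population** describes the modified intention-to-treat basis for all study analyses as "including all randomized patients, with the exception of withdrawn patients or those with missing outcome data". Patients randomized in error are also left out. An extreme outcome value is not among the listed reasons.
- **Table 2** classes "Units of RBCs transfused", together with plasma, cryoprecipitate and platelet transfusions, as continuous. Under Continuous outcomes these are "compared using linear regression".
- **Remedies that change the model** are already offered. Continuous outcomes allows a log scale and adds: "If a logarithmic transformation is not satisfactory other analysis or presentation methods will be sought". Model assumptions proposes alternatives, for example "by applying a logarithmic transformation or fitting a two-part mixed model for semi-continuous data".

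**The concern.** For an outcome measured once, removing the observation removes the randomized patient from that comparison, and the reason is a value recorded after randomization. Red-cell units are the direct product of the two strategies, so allocation can influence who is removed. If the strategies differ in the upper tail, removal is unequal between arms and the estimate describes a subset defined by outcome rather than everyone randomized.

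Without a cut-off, a data-error check or blinding, the choice of which patients to drop can be made after seeing the data. The reader is not guaranteed a full-data result for comparison.

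Genuine extreme values are plausible here. In the section on pre-specified ancillary analyses, the authors foresee that patients given many red-cell units may be outliers and make models fit badly. That section's restriction, with ten units as its example, applies only to the observational analyses. It still shows that such counts were expected in a variable that is also a secondary outcome of the randomized comparison.

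**Working it through.** **The plan's own figure.** The article gives no number for this rule. Its one design figure, 1,468 patients for 17% v 11% with 90% power and two-sided 5%, reproduces exactly with a continuity correction (734 per arm). The present point does not affect it.

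**Which outcomes the rule can reach.** Binary outcomes take two values, so there is no extreme value to remove. That leaves units of blood products, and possibly durations of stay and the EQ5D scores.

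**Assumptions.** The article gives no unit distributions. Everything below assumes 1,000 patients per arm (half of the 2,000 target) and invented distributions. The cut-offs are also assumed, since the rule has none.

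**Step 1: effect on one arm's mean.** Removing m patients with u units each from an arm with mean b shifts the mean by −m(u − b)/(1000 − m). For b = 1.5 and 2.5:

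- m = 5, u = 15: 5 × 13.5/995 = 0.07 and 5 × 12.5/995 = 0.06 lower
- m = 10, u = 20: 10 × 18.5/990 = 0.19 and 10 × 17.5/990 = 0.18 lower
- m = 20, u = 30: 20 × 28.5/980 = 0.58 and 20 × 27.5/980 = 0.56 lower

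**Step 2: simulation with zero-inflated negative-binomial units** (1,500 runs, Welch test; mean difference, with patients removed per arm in brackets):

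| Scenario | All values | Cut above 10 units | Cut above 3 SD |
|---|---|---|---|
| 90% transfused in both arms; mean 2.3 v 2.6 units if transfused | 0.27; power 73% | 0.17 (10 v 19); power 50% | 0.15 (16 v 27); power 43% |
| 90% v 60% transfused; same distribution if transfused | −0.75 | −0.70 (16 v 11) | −0.67 (27 v 18) |
| Identical arms | rejects 4% | rejects 5% | rejects 5% |

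Attenuation in the first row is 1 − 0.166/0.270 = 39% and 1 − 0.147/0.270 = 46%. In the second row it is 1 − 0.697/0.753 = 7% and 1 − 0.673/0.753 = 11%, and every run stayed significant.

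**Step 3: a small group of heavy bleeders.** Usual means are 1.3 (restrictive) and 2.0 (liberal); bleeders average 15 units. Full-data means follow by hand; trimmed results (above 10 units removed) come from simulation.

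- Bleeders 3% v 1%: 0.97 × 1.3 + 0.03 × 15 = 1.71; 0.99 × 2.0 + 0.01 × 15 = 2.13; difference −0.42. Trimmed −0.64, which is 0.22/0.42 = 52% too large.
- Bleeders 1% v 3%: 0.99 × 1.3 + 0.01 × 15 = 1.44; 0.97 × 2.0 + 0.03 × 15 = 2.39; difference −0.95. Trimmed −0.68, about 29% too small.
- Equal bleeders: −0.68 in simulation, trimmed −0.66, about 3%.

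**Step 4: the same three cases on log(units + 1)**, with negative-binomial dispersion 2. The ratio moves from 0.82 to 0.80, from 0.76 to 0.79, and stays at 0.79. On the log-difference scale, before rounding, that is about 18% larger, 13% smaller and no change.

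**The case against.** The best defence has four parts.

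1. **The main result is safe.** The primary outcome is binary and analysed by logistic regression. This stands. A reader might infer that the rule endangers the trial's principal conclusion; the documents do not support that.
2. **Model changes are already planned.** The sentence before the rule offers a transformation or a two-part model, which suits zero-heavy unit counts, so exclusion may have been meant as a last resort. This stands in part. The remedies are there, but the text does not put them first, and the exclusion sentence has its own trigger and its own mandatory wording.
3. **The large percentages are constructed.** The 52% and 29% need a threefold difference between arms in heavy bleeders, a ten-unit cut that the article mentions only for the ancillary analyses, and an untransformed scale. This stands. They show what could happen under assumption, not what to expect.
4. **The conflict over the population is partly formal.** The Patient population section defines who is analysed, whereas the rule removes observations from a particular model. That is fair for EQ5D, where a patient may keep other time points. For units measured once, the patient leaves that comparison altogether.

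A reader might also infer that the values to be removed are known to be real, or that false positives would increase. The article says neither that the values are verified nor that they are errors. With identical arms, the symmetric cut-offs tried left rejection at about 4–5%.

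**Conclusion.** The point holds for the secondary outcomes. The plan requires exclusion triggered by fit, does not confine it to errors, and makes the check on its effect optional. This goes beyond the exclusions in the Patient population section.

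The harm is a changed estimand, unequal removal when the arms differ in the upper tail, and discretion exercised after the data are seen. A material distortion is possible, not shown. Under the assumptions above it ranges from about 3% with equal shares of heavy bleeders, through 7–11% when the strategies differ mainly in the share transfused, to roughly 40–50% of a raw mean difference when the upper tails differ. It was smaller on the log scale in the cases tried. The direction cannot be known in advance, and all sizes depend on the assumed distributions and cut-offs.

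The Discussion says the plan has since been executed. It acknowledges marginal mean imputation as inappropriate but does not mention this rule. The article does not show whether any value was in fact excluded, and it should not be read as saying so.

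**What to change.** Reverse the default in Model assumptions:

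- Keep all verified values in the main analysis.
- If the fit is poor, change the model: use the log transformation or two-part model already named, or a count, rank-based, or robust or bootstrap method, with the planned adjustment for operation type and centre where the method allows.
- Correct or remove only confirmed data errors, decided blind to allocation.
- Report any outlier exclusion only as a labelled sensitivity analysis.

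Because the analysis has been run, the report should state for each affected outcome whether values were excluded, how many in each arm and why, and give the full-data result wherever any were. The trials unit's plan template, already revised for mean imputation, should be changed in the same way.

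The cost is a change of wording and, for some outcomes, a different regression command. Confidence intervals for some secondary outcomes will be somewhat wider, and a change of model may change the effect measure reported. The sample size is unaffected.
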